## Abstract

The importance of patient centricity and keeping the patient at the heart of research design is now well recognised within the healthcare community. The involvement of patient, caregiver and clinician representatives in the study design process may help researchers to achieve this goal and to ensure robust and meaningful data generation. Real-world data collection allows for a more flexible and patient-centred research approach for gaining important insights into the experience of disease and treatments, which is acutely relevant for rare diseases where knowledge about the disease is more likely to be limited. Here, we describe a practical example of a patient-centric, multi-stakeholder approach that led to the co-design of a prospective observational study investigating the lived experience of adolescents with the rare disease, X-linked hypophosphataemia. Specifically, we describe how the knowledge and expertise of a diverse research team, which included expert physicians, research and technology specialists, patients and caregivers, were applied in order to identify the relevant research questions and to ensure the robustness of the study design and its appropriateness to the population of interest within the context of the current clinical landscape. We also demonstrate how a structured patient engagement exercise was key to informing the selection of appropriate outcome measures, data sources, timing of data collection, and to assessing the feasibility and acceptability of the proposed data collection approach.

## Introduction

Patient-centred medicine development, involving patients and health service end-users, is now considered to be integral to the development of new treatments [1]. With the existing framework of medicine development being criticised for failing to sufficiently focus on patients, the eventual recipients of medicines [2–5], it is widely acknowledged that the patient should be placed at the centre of research design [6]. Multistakeholder co-design of research that includes patients and/or their caregivers, treating physicians and methodology specialists may be more resource intensive, but it not only offers an important opportunity to amplify the patient voice in a robust and structured manner but also ensures that real-world observational studies address questions of significance to those who will be impacted by or need to make decisions based on the study’s findings [7, 8].

International initiatives and consortia [9] have produced best practice guidance to guide patient centricity in research and to facilitate the implementation of patient-relevant outcomes, according to recommended and robust methodology [10–13]. It is also common for scientific journals and ethics committees to require evidence of patient involvement in research approaches prior to approving content. Furthermore, it has been suggested that engaging patients in the study design process may lead to later efficiencies; for example, by reducing the need for protocol amendments and/or improving rates of enrolment, adherence or retention [14].

Not only are patient-centred and co-design approaches growing in importance, real-world evidence continues to attract interest for the evaluation of new medicines [15, 16]. Alternative methods of data collection that extend beyond the randomised controlled trial (RCT) are being adopted more readily, such as registries, prospective observational studies, mixed-methods research and qualitative interviews [8]. Although the RCT remains the gold standard for establishing treatment efficacy and safety for regulatory purposes, an understanding of how patients experience their disease and treatments in real life is critical to continue to gather evidence of the value of medicines. Real-world data capture is particularly important in rare diseases, where there may be little or no published information on the natural history or course of the disease. The capture of patient experience data with sufficient rigour therefore allows for a better understanding of the real world and the patient-specific impact of new therapies [17].

Given this evolving research landscape, case examples of patient-centric, co-design approaches become increasingly noteworthy, particularly in the rare diseases. To that end, this article describes an example of a patient-centric, multistakeholder co-design approach for a prospective observational study investigating the lived experience of adolescents with a rare disease, X-linked hypophosphataemia (XLH) (NCT05181839). Our approach involved the early partnership of a diverse research team to inform the research questions and methodology. The variety of perspectives were gathered from relevant stakeholders, including patient-centred outcome research specialists, adolescents with XLH, a caregiver of an adolescent with XLH, expert physicians from across Europe and specialist technology providers (Fig 1). The multidisciplinary input to the research design was intended to enable the generation of robust, meaningful and patient-centred outcomes for this rare disease population.

**Fig 1 pone.0295080.g001:**
[figure not shown]
Overview of stakeholders involved in co-design of mixed-methods real-world study about the lived experience of adolescents with XLH at the end of skeletal growth.

We took a stepwise approach to developing and finalising the research study in adolescents with XLH, which started with defining the research questions and methodology (*Section 1*). Our description of the final study design and the multi-stakeholder involvement in each subsequent component is presented in the following sections, structured according to the PICOT framework: 2.) *Population (P)*, 3.) *Intervention (I)*, 4.) *Comparison (C)*, 5.) *Outcomes (O)* 6.) *Time / duration (T)* [18, 19].

## Materials and methods

### Defining the research questions and methodology

Our overall research aim was to understand the lived experience of adolescents with XLH at the end of skeletal growth, a crucial phase during the adolescent’s transition to adulthood. XLH is a rare, genetic, life-long disease that is associated with progressive accumulation of multiple musculoskeletal features that evolve across the patient’s lifetime [20–23]. Some knowledge of the disease burden for children and adults exists [24–27]. However, data are limited for adolescents with XLH. Furthermore, medical management of adolescents varies between countries [28]. For these reasons, adolescents’ experiences of XLH and the impact of treatment at the end of skeletal growth were considered to be an evidence gap worth investigating. Traditionally, treatment for children and adolescents with XLH has been oral phosphate and active vitamin D analogues; however, in February 2018, burosumab, a recombinant human monoclonal immunoglobulin G1 antibody that inhibits fibroblast growth factor 23 (FGF23), received European Medicines Agency approval for individuals aged 1 year or older with radiographic evidence of bone disease and adolescents with growing skeletons [29]. This approval was subsequently expanded in September 2020 to include older adolescents who had stopped growing, as well as adults, offering a new treatment option targeting the underlying pathophysiology of XLH [30]. Given the changing treatment landscape and known variation in treatment pathways for adolescents with XLH across different geographical locations, the research team acknowledged the importance of studying the experiences of adolescents in relation to burosumab treatment as part of the study.

As well as a lack of data on adolescents’ experiences, very little is known about the caregivers of adolescents with XLH during the period of ending skeletal growth. Although there is some literature on the experience of caregivers of people with other rare bone disorders [31–34], there is a dearth of literature about the experience of caregivers of adolescents with XLH, particularly relating to during the period of ending skeletal growth. An understanding of the caregiver experience may allow for increased knowledge of the impacts of caring for an adolescent with XLH, which in turn may identify the wider support requirements of caregivers. Hence, the main research questions to investigate were defined as:

**What is the experience of adolescents with XLH as they approach the end of skeletal growth while receiving treatment with burosumab**?

**How do the experiences of adolescents with XLH vary in the 6 months following end of skeletal growth according to treatment received**?

**What is the experience of caregivers at the time that the adolescent with XLH reaches the end of skeletal growth**?

Next, the most appropriate research methodology to address the research questions was identified as a mixed-methods approach, which is the combination of quantitative and qualitative data for the purpose of increasing the breadth and depth of understanding [35]. It is most suitable when a quantitative or qualitative methodology is inadequate by itself to address the study purpose [36]. When considering the lived experience of XLH, it was apparent that quantitative data on symptoms, activity, duration and intensity, alongside pharmacodynamics data, would illuminate disease impact over the study period, whereas qualitative data via interviews would complement and expand understanding of the quantitative findings. A more complete understanding of the lived experience of adolescents during the study period would therefore rely on the totality of evidence derived from both quantitative and qualitative data.

Furthermore, the mixed-methods approach is underpinned by a pragmatic research paradigm, which proposes that researchers adapt their methodological approach for the particular problem being investigated [35]. Importantly, assessment of individual experience is vital, whilst maintaining flexibility to embrace both objective and subjective knowledge [37, 38]. Given the rare nature of XLH and limited available knowledge about the treatment-related experiences of adolescents in particular, a degree of flexibility was needed and therefore a mixed-methods design was considered to be the most appropriate choice.

An observational, prospective design was selected to examine the lived experiences of adolescents during the period occurring immediately before and after the end of skeletal growth and to describe any treatment-related variation in a real-world clinical setting. A fully integrated, convergent mixed-methods design was thus deemed to be optimal for addressing the research questions, with both qualitative and quantitative data collected separately throughout the study and later merged for an overall interpretation [39].

### Study population (P) & study setting

#### Study population

The study population is that which best informs the research question, ensuring rich and relevant data, as well as enabling transference of the study findings to similar contexts [40]. Following discussion with treating physicians, the target population was defined as adolescents aged 12–⁠⁠17 years with a confirmed diagnosis of XLH (documented diagnosis of XLH in medical records, and evidence of at least one of the following: hypophosphataemia and/or impaired phosphate reabsorption due to elevated FGF23; PHEX mutation) who had been treated with burosumab for at least 12 months and were, in the opinion of their treating physician, approaching the end of skeletal growth (based on the treating physician’s routine growth tracking methods). Adolescents who were non-adherent to treatment, defined as missing ≥2 injections of burosumab in the previous 12 months, and those scheduled for orthopaedic surgery during the study, were considered to be important to exclude as these criteria could bias study outcomes.

A sample size of up to 30 adolescents was considered to be sufficient for this mixed-methods study, which is not hypothesis testing [41, 42]. Although some heterogeneity is expected, recruiting up to 30 subjects should represent the population sufficiently to allow for analyses according to treatment after the end of skeletal growth. This sample size was also considered to be feasible from a practical perspective, following consultation with potential participating specialist paediatric centres and expert treating physicians, in terms of the likely numbers of eligible adolescents at those centres. Purposive sampling was deemed to be appropriate, whereby physicians would use their knowledge to identify adolescents that met inclusion criteria [41]. This approach was considered to be feasible, as well as appropriate, to the research question and was expected to generate data that was generalisable to similar contexts.

Caregivers will be included in the study if they are a parent or guardian who provides day-to-day support or care for the adolescent with XLH who is taking part in this study. The caregivers in the sample will be interviewed about their experiences and support needs as a principal caregiver of an adolescent with XLH. It was determined that a sample of 15 caregivers would likely be more than sufficient to reach theme saturation, considering the homogeneity of the data to be collected [43]. To ensure sufficient geographical diversity, at least three representatives from each of the participating countries will be targeted for participation.

In this real-world study, a specific definition for the “end of skeletal growth” was not applied. Instead, the methods used to determine this stage aligned with local practices, which may vary across countries and among clinicians. However, clinicians were expected to document their approach to assessing the end of growth at the time of enrolment. This assessment included factors such as projected index dates, confirmed index dates, specific growth velocity thresholds, final height measurements or imaging results. Additionally, it is important to note that the prediction of “4 weeks before the end of skeletal growth” was determined by clinicians.

#### Study setting

The research literature indicates that the study setting should be accessible, appropriate for recruitment of the study population, and have staff at the study centre who are interested in and able to support the conduct of the research project [41]. Well-established specialist centres in the UK and across Europe that treat adolescents with XLH with burosumab were deemed to be suitable for inclusion and were subsequently approached by the study sponsor. An important consideration for centre inclusion was their potential to recruit enough eligible participants. The lead physicians at these specialist centres were informed of the purpose of the study, its methodology and the mutual role that centres would play in study design, conduct, analysis and reporting.

### Intervention

At the time of designing the study, burosumab had been studied in pivotal RCTs for ages 1–12 years, as well as in adults (aged 18–⁠65 years) [44–48]. The initial indication for burosumab in Europe (February 2018) was for the treatment of XLH in children aged 1 year and older with growing skeletons and radiographic evidence of bone disease. The indication was extended in September 2020 for the treatment of XLH in children and adolescents aged 1–17 years with radiographic evidence of bone disease, and in adults, thus enabling adolescents to be treated after the end of skeletal growth [30]. As this is a real-world observational study, the decision to continue burosumab will depend on reimbursement approvals in the different countries, with some patients required to discontinue treatment with burosumab at the end of skeletal growth and instead be offered alternative treatment, such as oral phosphate and active vitamin D.

### Outcomes

Appropriate outcomes relevant to the population need to be identified to sufficiently answer the research questions. In other words, ***what*** data should be collected (i.e. the **data variables**), ***how*** should the data be collected (i.e. the **data sources**), and ***when*** should data be collected to be most informative but also not overburden the study participants (i.e. the **timing**).

Data collection from medical records would be required to understand the characteristics of this population and key pharmacodynamics and clinical information relating to the XLH disease course. However, for meaningful insights into the experiences of adolescents with XLH, the majority of the data should be derived directly from the patient. To assist with this aspect of the study design, adolescents with XLH were invited to participate in a structured patient engagement exercise to inform the selection of appropriate outcome measures, data sources and timing, and to assess the feasibility and acceptability of the proposed method of data collection. Principal investigators would not have access to data to identify individual patients during or after data collection. The patient advocacy group (PAG) XLH UK was approached to help with recruiting adolescents with XLH to participate in a 60-minute, one-to-one telephone interview with experienced interviewers from OPEN Health. A structured interview guide was developed with input from expert physicians to gather insights into adolescents’ experiences of living with XLH, their treatment and their opinions of the proposed study. Four adolescents consented to participate in the interviews and provided insights into the selection of outcomes and data sources in the study [49].

The interviews verified insights from clinical trials that symptoms of pain, stiffness and fatigue were important to measure and likely to be impacted by treatment. The physician experts reported that it would be relevant to capture the location of pain and use of analgesia, so these outcomes were also incorporated into the study design. The collection of data before and after the end of skeletal growth would then enable an evaluation of any changes in symptoms depending on the treatment regimen received after the end of skeletal growth.

In the interviews, adolescents described how their ability to participate in social and leisure activities was affected by their symptoms (S1 Fig). Participants reported being slower at keeping up with their friends; for example, when climbing stairs, catching the bus and during physical education at school. They also stated that, although they felt more tired/fatigued than their friends and found activities more difficult, they continued nonetheless to take part in them. Overall, the discussion suggested that there was a significant interplay between physical activity levels and symptoms of XLH (such as pain, stiffness and fatigue), to warrant monitoring activity closely in order to interpret changes.

To capture data on the duration and level of physical activity, as well as their participation in social and leisure activities, a wearable device was used, as well as collecting information on their participation in social and leisure activities. To further understand any wider impact of symptoms, the research team considered it appropriate to collect information on any time missed from school/work, as well as utilisation of healthcare resource (Fig 2).

**Fig 2 pone.0295080.g002:**
[figure not shown]
Concepts derived from patient interviews and following discussions with the research team.

The adolescents did not consider that there was a notable impact on sleep quantity or quality. However, the view of the expert physicians consulted on the study design was that sleep may be an interesting variable to measure, particularly given that this is something anecdotally reported as being affected due to levels of pain experienced (Fig 2). Given that the subjects would be wearing a device to capture activity levels in the daytime, and such devices have been used to collect data in the night, the research team proposed that participants should be given the option to wear the device at night to gain a proxy measurement of sleep quantity and quality activity data. Qualitative interviews would also provide another opportunity for adolescents to express their own views on sleep quality.

In addition, the team considered measuring the overall physical, emotional and social well-being of the subjects, with a general health-related quality of life outcome (HRQoL) measure (Table 1 and Fig 2). The EuroQol-5 dimensions-Youth (EQ-5D-Y) was chosen by the study team, as a short, widely used and well-validated HRQoL tool for the youth age range [50, 51].

**Table 1 pone.0295080.t001:** Overview of data collection schedule for quantitative and qualitative data relating to XLH symptoms and activity levels.

Topics	Endpoints	Source	Before end of skeletal growth^a^ (4 weeks)			After end of skeletal growth^b^ (26 weeks)		
			Daily	End of each week	At start of 4-week period	Daily for 1 week every 4 weeks	End of week for other study weeks	End of post-index period (Weeks 21–25)
**Pain**	• Worst pain	App						
	• Location							
	• Use of analgesia		X			X	X	
**Stiffness**	• Worst stiffness	App	X			X	X	
**Fatigue**	• Worst fatigue	App	X			X	X	
**Physical activity**	• Daytime duration	Wearable	X			X		
	• Daytime intensity							
**Social and leisure activities**	• Participation in social & leisure activities	App		X			X	
**School/work**	• Missed time	App		X			X	
**HCRU**	• Scheduled and emergency appointments	App		X			X	
**HRQoL**	• EQ-5D-Y	App			X			X
**Sleep**	• Duration	Wearable						
	• Quality		X			X		
**Adolescent experience**	• Lived experience	Telephone interview			X			X
**Caregiver experience**	• Identifying support needs	Telephone interview						X

EQ-5D-Y: EuroQol-5 dimensions-Youth; HCRU: Healthcare resource use; HRQoL: Healthcare-related quality of life; XLH: X-linked hypophosphataemia.

^a^Data will be collected prospectively for a 4-week period (as agreed in advance with the adolescent) to occur 4–12 weeks prior to the predicted date of end of skeletal growth.

^b^Data will be collected prospectively for 26 weeks from the confirmed date of end of skeletal growth (index date).

Given the nature of the selected endpoints and the age of the study participants, the research team considered that the outcomes could be measured using a bespoke designed smartphone app (Atom5^™^; Aparito, Wrexham, Wales, UK), as well as a wearable device (Garmin Vivosmart4^®^; Garmin, Ltd., Olathe, KS, USA). During the patient engagement exercise, adolescents were asked for their opinions about the use of smartphone apps and wearable devices (e.g. commercially available fitness watches) for data collection. All of the adolescents verified that they would be happy to input data via a smartphone app and they also expressed openness to wearing a wrist-based fitness device to track activity during the day, with the majority being happy to use this at night. This feedback endorsed the wider research team’s view around the wearable being an optimal and non-invasive tool for capturing data on physical activity levels and for sleep monitoring.

Finally, to collect qualitative data on the experiences of adolescents that would sufficiently complement and expand understanding of the quantitative findings, the research team included two one-to-one interviews with the adolescents before end of skeletal growth and at 6 months following end of skeletal growth as part of the overall study design. Interviews, based on a semi-structured discussion guide, would allow for an in-depth understanding of symptoms and an exploration of the social and emotional impacts of experiences, coping strategies and future aspirations, and provide further context to questions that are being asked during the app-administered surveys. This particular point was highlighted as being important by our caregiver member of the research team who was able to verify each of the outcomes identified by the adolescents from a patient and caregiver perspective.

By scheduling an interview at the end of the study, it would be possible to explore changes in symptoms and experiences over time and to examine the relationship between these changes on social and emotional experiences. In addition to interviewing adolescents with XLH, a separate interview with the adolescent’s caregiver during this same period following end of skeletal growth will provide an opportunity to gain insight into caregiver experiences.

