### Data analyses

This is a mixed-methods research study, whereby descriptive analyses of quantitative data (medical records, app, wearable device and EQ-5D questionnaire) will be synthesised with qualitative data (interviews) to describe the lived experience of XLH for adolescents at the end of skeletal growth in the pre-index and post-index periods [39]. To address missing data, there will be no imputation for symptom diary and wearable parameters, with a threshold of 3 days’ data in a week being required to calculate a weekly average. A sensitivity analysis will be performed using a minimum of 4 days required to calculate a weekly average score for symptoms and wearable parameters.

Distributions and descriptive statistics of central tendency (medians and arithmetic or geometric means) and dispersion (standard deviation, interquartile range [IQR], range) will be presented for quantitative variables. Any categorical variables will be described with frequencies and percentages; where appropriate, distributions, modes, medians, IQR and range will be reported. Daily measurements (e.g. pain, stiffness and fatigue measurements collected using the app) will be summarised per adolescent for key time-points pre- and post-index, to aid interpretation of change post-index and individual data trends visualised over time. EQ-5D-Y scores will be converted to a single utility value during data analysis. Visual Analogue Scale and scores for each of the five domains assessed in the EQ-5D-Y (mobility, self-care, usual activities, pain/discomfort and anxiety/depression) will also be summarised separately. Statistical analyses will be carried out using Stata version 14.2 (StataCorp LLC).

Qualitative/thematic data analyses will be conducted using the Framework approach, engaging the use of matrices to manage data, allowing for easy movement across the whole dataset in order to explore patterns in the themes across different groups of participants, as well as trajectories within individual participants [52]. Analyses on patient data will be conducted cross-sectionally at baseline and for the post-index interview to allow for analysis between individuals, in addition to being analysed longitudinally for each individual, in order to capture a narrative for each adolescent and the trajectory of change. Carer data will be analysed separately.

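### The baseline and the follow-up sample different parts of the year, so within-adolescent changes in activity, participation and missed school can partly reflect the calendar; a term/holiday flag is a cheap improvement

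*Protocol article*

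**What the plan says.** The schedule is in Table 1 of the protocol article and its footnotes.

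- **Baseline** (footnote a): "Data will be collected prospectively for a 4-week period (as agreed in advance with the adolescent"), placed "to occur 4–12 weeks prior to the predicted date of end of skeletal growth".
- **Follow-up** (footnote b): "Data will be collected prospectively for 26 weeks from the confirmed date of end of skeletal growth (index date").
- **Endpoints.** Wearable activity, participation in social and leisure activities and missed school/work time are listed both before and after index. The Outcomes section gives the intention to "collect information on any time missed from school/work". It also reports that the adolescents interviewed were slower than friends "when climbing stairs, catching the bus and during physical education at school", and two of these examples are typical of the school day.
- **Use of the data.** For symptoms, Outcomes says that collecting before and after "would then enable an evaluation of any changes in symptoms depending on the treatment regimen received after the end of skeletal growth". Under Data analyses, daily measurements "will be summarised per adolescent for key time-points pre- and post-index", and individual trends are plotted over time.

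The Time section, Data analyses and the limitations in the Discussion do not mention season, school terms or holidays.

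**The concern.** Three of the endpoints plausibly depend on the calendar. School cannot be missed in a week without school. Activity and leisure in adolescents can differ between term and holiday and between summer and winter. One short block before index is set against half a year after it, so the two periods cannot cover the same part of the year.

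A baseline in a summer holiday could be followed by an apparent fall in activity, and a winter baseline by an apparent rise, whatever happens to the disease or the treatment. This matters most for the per-adolescent summaries, because staggered start dates do not cancel season within one person.

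It also touches the second research question, on how experience varies by treatment after the end of growth. The sample is at most 30, split by treatment received. The Intervention section says that continuing burosumab depends on reimbursement in each country. Start months and school calendars therefore need not match between treatment groups.

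**Working it through.** The plan has no figure of its own to reproduce. The sample size rests on feasibility and mixed-methods practice, and no SD or effect size is given. The check is calendar arithmetic on the schedule, followed by two illustrations.

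**Inputs from the protocol article.** Baseline of 4 weeks, 4 to 12 weeks before the predicted date; follow-up of 26 weeks from the confirmed date (Table 1 footnotes); up to 30 adolescents (Study population).

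**Assumptions.** Confirmed date equals predicted date; a year of 52.18 weeks; index dates spread evenly over the year. The yearly cycle and the school calendars below are also assumed.

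**1. Where the opposite season falls.** If the whole block lies in weeks −12 to −4, its midpoint m is between −10 and −6. Opposite season = m + 52.18/2 = m + 26.1.
- m = −10: week 16.1
- m = −6: week 20.1
- If the 4 to 12 weeks refer to the start of the block, the latest midpoint is −2, giving week 24.1, still inside follow-up.
- If the confirmed date is 8 weeks later than predicted, weeks 16.1 to 20.1 become 8.1 to 12.1.

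**2. How much of follow-up is out of phase.** A quarter-year is 52.18/4 = 13.0 weeks. Counting follow-up weeks at least that far from the baseline midpoint:
- m = −10: 23 of 26 (88%)
- m = −6: 19 of 26 (73%)
- m = −2 (wider reading): 15 of 26 (58%)

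**3. Size within one adolescent.** Take a yearly cosine of amplitude A. Averaging over L weeks multiplies it by sin(πL/52.18)/(πL/52.18), which is 0.99 for 4 weeks and 0.64 for 26 weeks. With gap g between window midpoints, the largest difference over all start dates is A√(0.99² + 0.64² − 2 × 0.99 × 0.64 × cos(2πg/52.18)).
- m = −10, g = 23: 1.60A, SD over start dates 1.60A/√2 = 1.13A
- m = −6, g = 19: 1.49A, SD 1.05A

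**4. Size between groups.** With evenly spread index dates the expected artefact is zero. Its SD for a difference between two groups of n is SD × √(2/n).
- 15 v 15: 1.05A to 1.13A × 0.365 = 0.38A to 0.41A
- 5 v 5: 1.05A to 1.13A × 0.632 = 0.66A to 0.71A

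**5. Holidays.** Three assumed calendars, whole block in weeks −12 to −4:

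| Assumed holidays per year | Baselines with no holiday | At least half holiday | All holiday | Holiday share of follow-up |
|---|---|---|---|---|
| 6-week summer + 7 other weeks | 40% | 25% | 6% | 15–35% |
| 9-week summer + 3 | 60% | 25% | 12% | 8–38% |
| 12-week summer + 3 | 54% | 31% | 17% | 8–50% |

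Within one adolescent the holiday share of baseline and follow-up can differ by up to about 0.9.

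**The case against.** The study tests no hypothesis. It plans interviews that give context to the app answers, and the Discussion expects the merging of qualitative and quantitative data to reveal reasons beyond treatment. That is a stated, informal safeguard. It stands in part: an interview before index and another at about six months may bring a holiday to light, but they cannot assign term or holiday status to each collection week. The article is also a condensed account, so the full protocol or analysis plan may contain an allowance.

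A reader might infer several stronger points, which the document does not support:

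- **That a holiday week is scored as zero missed school.** Table 1 gives only a topic label. The app question, its response options and its scoring are not shown.
- **That the adolescent's choice of weeks drives the problem.** With the whole block inside the window, choice moves it by at most 4 weeks (8 on the wider reading). Season is set mainly by the index date.
- **That the full opposite-season contrast is the expected effect.** Late follow-up against baseline would give up to 1.8A to 1.9A, but the column "End of post-index period (Weeks 21–25") applies only to EQ-5D-Y and the interviews. Activity, participation and missed time are collected throughout follow-up, and the early weeks are close in season to baseline.
- **That the treatment comparison is biased.** With evenly spread index dates the artefact averages to zero. The sites are in the UK and elsewhere in Europe, so their seasons are in phase. Differences in term dates are assumed. Treatment following country is a wider confounding issue.
- **That symptoms are affected too.** The sentence on change by treatment regimen concerns symptoms, and nothing in the document shows that pain, stiffness or fatigue follow the season.

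**Conclusion.** The point holds as a cheap improvement. The mismatch in time of year follows from the schedule itself. On either reading of the footnote, with accurate prediction, the opposite season falls inside follow-up, at about weeks 16 to 20 if the whole block lies in the window. Between 58% and 88% of follow-up weeks are at least a quarter-year out of phase with baseline.

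The within-adolescent artefact in the 26-week mean is at most 1.5A to 1.6A. The between-group artefact has mean zero and an SD of about 0.4A at 15 v 15, or about 0.7A at 5 v 5. These sizes rest on an assumed cosine, exact prediction and evenly spread index dates. A cannot be taken from the document, so whether the effect is material in absolute terms is unknown.

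It concerns how changes in activity, participation and missed school/work are read, and only the analysis described in this article.

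**What to change.** 1. Using collection dates and local school calendars, flag each collection week as term or holiday.
2. Show pre/post change in activity, participation and missed time for term weeks only, beside the all-weeks summary. Leave holiday weeks out of missed school.
3. Tabulate the calendar month of baseline by treatment group. Term-only summaries remove holidays but not summer against winter within term, so this table is still needed.
4. Name season as a limitation.

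A rule forcing the baseline into term time is not advised. Follow-up would still include holidays (8% to 50% under the assumed calendars), so the all-weeks summary would gain a one-directional bias. It would also split a cohort already recruiting since November 2021 between two collection rules.

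**Cost.** One extra set of descriptive tables and the work of matching dates to school calendars. This needs no new data from participants and can be done for everyone before the analysis planned for 2024. The term-only summary has fewer weeks. An adolescent with an all-holiday baseline has no term-only comparison: under the assumed calendars 6% to 17%, or about 2 to 5 of 30 (0.06 × 30 = 1.8; 0.17 × 30 = 5.1).
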